#### Telehealth consultation

Participants and their whānau (families) will be invited to attend a telehealth consultation with a staff member of the Hub. During the consultation, individuals will have the opportunity to discuss current commercial AID options in NZ, which at the time of this protocol development includes the Control-IQ system with the Tandem t: slim X2 insulin pump (Tandem Diabetes Care Incorporated, California, USA) and the CamAPS system (CamDiab Limited, Cambridge, England) with the mylife Ypsopump (Ypsomed Holding AG, Burgdorf, Switzerland). Other systems are commercially available in NZ but funded access is restricted so beyond the scope of this model of care. Following initial consultation, participants will select their preferred AID system including the compatible CGM. Two weeks of CGM data prior to AID commencement will be used as baseline glycaemic data. Participants will be provided with a pump start guide that includes information about starting AID, and will be used by clinical staff during education and participant follow up.

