## Methods

### Trial conduct

#### Study design

This is a quasi-experimental, single-arm study which will assess a new model of AID health care delivery in NZ. The new model of health care will be the remote Hub which will be deployed to provide prioritised national AID set up and support, before transferring participants back to their usual care teams after a maximum of 12 weeks (See Fig. 1 for summary of study design). The duration from referral to enrolment may vary depending on participants prioritisation score (outlined below in Sect. 2.3.2).

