#### Baseline

After completing consent, participants will then be directed to complete a range of online questionnaires (or on paper if unable to be completed online) including the diabetes treatment satisfaction questionnaire (DTSQ), EQ-5D, and the carbohydrate counting assessment tool.

If a participant has not had a routine biochemical review completed as part of their usual diabetes care in the past 12 months, a referral will be sent to the relevant laboratories where the participant is located for collection of samples to assess: urinary albumin: creatinine ratio, lipid and/or renal studies. A request for an updated HbA1c will be sent for all participants (either laboratory or point of care). Anthropometric data (weight, height and blood pressure) included in the referral will be used as baseline data.

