#### Preparation for commencement of AID

After selection of their preferred AID system, participants will be provided with a prescription for all equipment required prior to the pump-start training. Special Authority and prescriptions will be completed by clinical staff who have a prescribing authorisation. Prior to commencement of AID, the Hub clinical staff will determine the initial pump settings based on at least two weeks of CGM data, their recent insulin dose history, as well as physical and biochemical measurements collected at baseline. Pump start settings will be sent to the Pump Trainer at least one week prior to training.

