#### 12-weeks (primary end-point)

At 12 weeks, participants will be asked to complete the DTSQ change and EQ-5D questionnaires, and to attend their nearest laboratory for a final measurement of HbA1c. CGM data will be downloaded from participants’ online profile. Access to participant profiles will be retained on the study accounts to allow for remote review at 6-months for the purpose of data retrieval. Participants will be referred back to their usual care team at 12-weeks post AID start or earlier if stable (e.g., If TIR is > 70% or individualised TIR target is met with no significant hypoglycaemia or other concerns, the patient will be discharged before 12 weeks). This will involve a transfer of all CGM and HbA1c data back to their usual care teams to ensure optimal ongoing support. If for any reasons the Hub team do not believe discharge at 12 weeks is safe, then this will occur at a later date when appropriate.

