#### Intervention effectiveness

Intervention effectiveness of AID will be determined by estimating participants’ changes in standard glycaemic metrics between baseline and 12-weeks including: HbA1c, time in range ([TIR], 3.9 to 10.0 mmol/L [70 to 180 mg/dL]), time in tight range ([TING/TITR] 3.9 to 7.8 mmol/L [70 to 140 mg/dL]), time below range ([TBR] < 3.9mmol/L [< 70 mg/dL]), and time < 3mmol/L (< 54 mg/dL), > 10mmol/L (> 180 mg/dL) and > 13.9mmol/L (> 250 mg/dL). CGM metrics will also be assessed between baseline and 12-weeks, and again at 24-weeks (6 months) to determine whether any benefits are maintained following discharge, These include glycaemic management index (GMI), glycaemic outcomes differentiated as 24 h, day (0600–2359 h) and night (0000–0559 h), co-efficient of variation (CV_glucose_), and mean sensor glucose +/-SD.

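### For participants whose first CGM comes through the Hub, HbA1c change and time-in-range change probably measure different contrasts, yet both are pooled as the effectiveness of AID; the HbA1c method may also differ between visits

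*Protocol article*

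**What the plan says.** All references are to the protocol article; no statistical analysis plan is shown.

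- **Design** (Study design): "This is a quasi-experimental, single-arm study which will assess a new model of AID health care delivery in NZ".
- **Baseline HbA1c** (Baseline): after consent, "A request for an updated HbA1c will be sent for all participants (either laboratory or point of care". No window for the blood draw is given relative to CGM start or to Day 0.
- **Choice of CGM** (Telehealth consultation): "Following initial consultation, participants will select their preferred AID system including the compatible CGM".
- **Supply** (Preparation for commencement of AID): once the system is chosen, "participants will be provided with a prescription for all equipment required prior to the pump-start training". Hub staff then "determine the initial pump settings based on at least two weeks of CGM data", among other inputs, and the settings reach the trainer a week or more ahead of training.
- **Baseline CGM metrics** (Telehealth consultation): "Two weeks of CGM data prior to AID commencement will be used as baseline glycaemic data".
- **Follow-up HbA1c** (12-weeks): participants are asked "to attend their nearest laboratory for a final measurement of HbA1c".
- **Outcome label** (Intervention effectiveness): "Intervention effectiveness of AID will be determined by estimating" the changes in HbA1c, TIR and other CGM metrics from baseline to 12 weeks. The Statistical analysis section summarises these descriptively as change across the start of AID, with no split by prior CGM use.

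**The concern.** In a single-arm study the participant's own baseline is the only glycaemic comparator. The Statistical analysis section confirms this: national laboratory and CGM data do not exist for people outside the study. What a change means is therefore settled by what its baseline contains.

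HbA1c reflects the preceding months. TIR cannot be measured until CGM is worn. For someone who had no CGM before the Hub, the first baseline probably lies mostly before CGM start and the second necessarily lies after it. One label then covers two contrasts, and they are averaged with those of established CGM users, for whom the problem does not arise.

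New users are plausible. The Background gives lack of publicly funded CGM as a main barrier until October 2024, and prior CGM use is not an entry condition (Study population). At stake is what the reported HbA1c and TIR changes mean, and whether the two can be read side by side. Separately, a change of HbA1c method between visits would enter the within-person change for some participants.

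**Working it through.** **1. The plan's own figure.** Statistical analysis states more than 90% power at N = 500, two-sided alpha 0.05, standardised effect 0.15. For a paired change, power = Φ(0.15 × √500 − 1.96) = 91.8% (91.7% by the noncentral t). A proportion is estimated to within 1.96 × √(0.25/500) = 4.4 points. Both statements reproduce, and neither depends on this point.

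**2. Sequence for a new CGM user.** In the order of the sections: consent, HbA1c request, consultation, choice of system and CGM, prescription, two or more weeks of CGM data, settings sent one or more weeks before training, Day 0. If CGM is worn throughout, such a person has at least 2 + 1 = 3 weeks on CGM before AID starts.

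**3. What each change contains.** Let *c* be the fall in HbA1c from starting CGM and *A* the further fall from AID.

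| | HbA1c change | TIR change |
|---|---|---|
| Established CGM user | AID | AID |
| New CGM user | CGM plus AID | AID added to CGM |

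If a share *p* are new users, the pooled mean HbA1c fall is *A* + *p* × *c* (taking *A* as equal in both groups). TIR has no matching term to the extent that the CGM effect is already present in its two-week baseline.

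**4. Two readings of the label.** The Background defines AID as a system that includes a CGM. On that reading the HbA1c change is the intended quantity, and TIR change falls short of it for new users. The Statistical analysis section takes change across AID start. On that reading the TIR change is the intended quantity, and HbA1c change exceeds it by *p* × *c*. Neither reading makes both right for new users.

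**5. Size, on assumptions only.** The documents give neither *p* nor *c*. Values of *p* × *c* in HbA1c percentage points:

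| *p* | *c* = 0.2 | *c* = 0.4 | *c* = 0.6 |
|---|---|---|---|
| 0.1 | 0.02 | 0.04 | 0.06 |
| 0.3 | 0.06 | 0.12 | 0.18 |
| 0.5 | 0.10 | 0.20 | 0.30 |
| 0.7 | 0.14 | 0.28 | 0.42 |

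Two yardsticks:
- With an assumed SD of change of 1.0 to 1.5 points, the effect of 0.15 SD that the study is powered for is 0.15 to 0.23 points, so the upper part of the table reaches it.
- Against the 2.5-point fall that the Background cites from a trial in children and youth with above-target glycaemia, the range is 0.02/2.5 = 0.8% to 0.42/2.5 = 16.8%.

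**6. HbA1c method.** If a share *q* have a point-of-care baseline that differs on average by *m* from the laboratory value, the mean change shifts by *q* × *m*. With *q* = 0.40 and *m* = 2 to 4 mmol/mol (assumed), that is 0.40 × 2 = 0.8 to 0.40 × 4 = 1.6 mmol/mol, upwards or downwards. The documents give no share, size or direction.

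**The case against.** **AID includes CGM by definition.** The first objective concerns the Hub's effectiveness in starting AID, not the algorithm's gain over CGM. For a new user, HbA1c change across the whole package is then a legitimate result. This stands, and it rules out the stronger inference that the HbA1c fall is simply inflated. It does not reconcile HbA1c with TIR, because on the same reading TIR change leaves out part of the package.

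**The premises are partly inferred.** The article gives no date for the HbA1c draw, the order comes from the sequence of sections, and the schedule (Table 1) is not shown. Masking of the CGM is not mentioned. The baseline fortnight is not said to be the last one before AID. No figure shows that CGM alone helps within weeks. These limits stand. They matter less for HbA1c, since a sample taken soon after CGM start would still mostly reflect earlier glycaemia.

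**The detail may sit elsewhere.** The referral form collects diabetes history (Recruitment), which may include CGM use, and stratified tables commonly belong to the analysis plan. Their absence from the article is not the point. The article itself fixes both baselines and the single label, and a later plan can separate the groups only if the dates and methods were recorded.

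**The mismatch is largely unavoidable.** A person without CGM has no TIR until CGM is worn. This is true, so the remedy is to label and stratify, not to align the baselines. A reader might go further and confine statements about AID to established users, or require a laboratory HbA1c from everyone at baseline. The first would remove people with least prior access to the technology from the effectiveness statement. The second would burden the rural participants whom the Hub prioritises. Neither is needed.

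**Conclusion.** The point holds as a matter of interpretation. For new CGM users the two baselines probably lie on different sides of CGM start, so the pooled HbA1c and TIR changes do not estimate the same thing under the one label. Which of the two departs from the effect of AID depends on how AID is read, and this assumes that CGM by itself improves glycaemia. The size is unknown: 0.02 to 0.42 HbA1c points on the assumed inputs, and nil if few participants are new to CGM.

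The difference in HbA1c method is explicit in the text for anyone with a point-of-care baseline. Whether it biases the mean, and in which direction, cannot be told from the documents.

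A reader might infer that the study's main result or its power is compromised. It is not: the primary outcome is implementation effectiveness, these changes are secondary and descriptive, and the power statement reproduces.

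**What to change.** 1. Record for every participant whether CGM was in use before the Hub and its start date, and the date and method of each HbA1c.
2. Report HbA1c and CGM changes overall and separately for new and established CGM users, with the dividing rule set before the data are examined.
3. In the new-user stratum, describe the HbA1c change as *CGM plus AID* and the TIR change as *AID after CGM start*.
4. Repeat the HbA1c summary in participants with laboratory values at both times.

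The cost is a few data fields, one extra table and smaller strata with wider intervals. No visit, test or treatment changes.

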#### Preparation for commencement of AID

After selection of their preferred AID system, participants will be provided with a prescription for all equipment required prior to the pump-start training. Special Authority and prescriptions will be completed by clinical staff who have a prescribing authorisation. Prior to commencement of AID, the Hub clinical staff will determine the initial pump settings based on at least two weeks of CGM data, their recent insulin dose history, as well as physical and biochemical measurements collected at baseline. Pump start settings will be sent to the Pump Trainer at least one week prior to training.

#### Nutrition education

All individuals enrolled in the Hub will be required to complete a carbohydrate counting assessment tool online, prior to commencement of AID. For children 11 years or younger, parents will complete the assessment. Individuals with lower scores from the assessment, or those that for any reason have been identified to require dietetic follow up from the initial consultations, will be invited to attend either a structured group carbohydrate awareness education session or a one-on-one session led by a NZ Registered Dietitian. These education sessions will be optional and will occur independently to the timeline for AID start (e.g., participants may start AID prior to optional education session). Participants who attend the group sessions will be asked to complete a three question pre- and post- session self-efficacy questionnaire (each question scored on a five-point scale: How confident are you in your ability to accurately count the amount of carbohydrate in each of your meals? How important is carbohydrate counting, to you, for managing your diabetes? How confident are you in your ability to identify foods that contain carbohydrate?). Participants whose score indicates they should use fixed carbohydrate doses while awaiting Dietitian input, will be asked to complete a 3-day diet record using Easy Diet Diary to allow for calculation of fixed doses as per established and published methods [23, 36].

#### Commencement of AID (Day 0)

Participants and their whānau (families) will be invited to attend an in-person training session for commencement of AID. The training will be provided by a certified pump trainer from the pump supplier at a suitable location. To optimise resources, group training sessions will be held, however, individual training sessions will be provided where needed. Whilst in-person training sessions are encouraged, online AID training sessions will be arranged if required. Directly following the training session, participants will be contacted by a clinical staff member to provide support. Participants usual health care providers will be notified that the person is starting on AID.

#### Follow up

Once AID has commenced participants will have daily remote data review for the first two days (Day 1 and 2), one review in weeks two, three and four and one review during both the second and third months, ending at the end of the 12-week period. Follow up will be increased/decreased if clinically required and 24/7 technical support will be provided by the relevant diabetes technology company as per standard care. The content of the follow up sessions will be guided by each participants experiences and will focus on key topics of additional training used in standard care including, but not limited to: exercise, bolus adjustment, managing sick days, assessing and adjusting system settings, and optimising use of the AID system.

#### 12-weeks (primary end-point)

At 12 weeks, participants will be asked to complete the DTSQ change and EQ-5D questionnaires, and to attend their nearest laboratory for a final measurement of HbA1c. CGM data will be downloaded from participants’ online profile. Access to participant profiles will be retained on the study accounts to allow for remote review at 6-months for the purpose of data retrieval. Participants will be referred back to their usual care team at 12-weeks post AID start or earlier if stable (e.g., If TIR is > 70% or individualised TIR target is met with no significant hypoglycaemia or other concerns, the patient will be discharged before 12 weeks). This will involve a transfer of all CGM and HbA1c data back to their usual care teams to ensure optimal ongoing support. If for any reasons the Hub team do not believe discharge at 12 weeks is safe, then this will occur at a later date when appropriate.

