### Outcomes

The primary outcome of this study is to assess the implementation effectiveness of the Hub. Secondary outcomes of this study include intervention effectiveness, safety and acceptability, psychosocial measures, nutrition education effectiveness, cost-effectiveness and clinical staff self-efficacy and intervention acceptability.

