#### Diabetes treatment satisfaction

The DTSQs and the DTSQ-change (DTSQc) are validated self-report measures of a participant’s current treatment satisfaction, and consist of an 8-item adult version (18 + years of age) and 12-item teen version (13–17 years of age), and a 14-item parent version that measures a parent’s satisfaction with their teen’s (ages 13–15 years) diabetes treatment [38]. The DTSQs Parent/Teen are used at baseline and follow-up to provide a ‘difference’ score for comparison. Scores can be compared between teens and their parents’ reports. The DTSQc has been developed to overcome potential ceiling effects, where respondents score near-maximum satisfaction at baseline and would therefore show little or no improvement at follow-ups [38]. Participants will complete the DTSQs at baseline and both the DTSQs and DTSQc at 12-weeks, to assess changes baseline, end of study and change in diabetes treatment satisfaction.

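### The 12-week visit lists only the change form of the DTSQ, while the outcome section requires the status form as well; the two passages must be reconciled

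*Protocol article*

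**What the plan says.** Four places in the protocol article bear on this outcome.

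- **Outcomes.** "Secondary outcomes of this study include intervention effectiveness, safety and acceptability, psychosocial measures" are listed, so treatment satisfaction falls under a named secondary outcome.
- **Baseline.** Participants complete a set of online questionnaires, "including the diabetes treatment satisfaction questionnaire (DTSQ), EQ-5D, and the carbohydrate counting assessment tool". The DTSQ is named here without its version.
- **12-weeks (primary end-point).** At this visit "participants will be asked to complete the DTSQ change and EQ-5D questionnaires". The change version is named; the status version is not mentioned.
- **Diabetes treatment satisfaction.** "Participants will complete the DTSQs at baseline and both the DTSQs and DTSQc at 12-weeks". The stated purpose is "to assess changes baseline, end of study and change in diabetes treatment satisfaction". The section also says "The DTSQs Parent/Teen are used at baseline and follow-up to provide a ‘difference’ score for comparison", and it gives the reason for the second form: "The DTSQc has been developed to overcome potential ceiling effects".

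The study schedule (Table 1) is not reproduced in the text available for this review.

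**The concern.** The procedures section and the outcome section both state what is collected at 12 weeks, and they do not agree. Staff who assemble the questionnaire set from the 12-week section would have no reason to include the status form, because that section picks out the change version by name.

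At stake are two quantities that the outcome section plans to report: the level of satisfaction at the end of the study, and the difference between baseline and follow-up status scores, which the section names for the parent and teen versions. Both need a status score at 12 weeks. CGM data can be retrieved from the study accounts after the visit. A participant's satisfaction at 12 weeks can only be recorded at about that time, and the section on the 6-month review describes CGM data and no questionnaires. An analysis plan cannot restore a form that was never given.

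**Working it through.** No sample size, power or event figure bears on this point, so the check sets the passages side by side.

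**Step 1: which forms each part of the document asks for.**

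| Time | Baseline and 12-week procedure sections | Diabetes treatment satisfaction section |
|---|---|---|
| Baseline | DTSQ, version not named | DTSQs |
| 12 weeks | DTSQc | DTSQs and DTSQc |
| DTSQ forms in total | 1 + 1 = 2 | 1 + 2 = 3 |

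The discrepancy is 3 − 2 = 1 form: the status version at 12 weeks.

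**Step 2: what each planned quantity needs.**

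| Planned quantity | Forms needed | Available under the 12-week section | Available under the outcome section |
|---|---|---|---|
| Baseline level | DTSQs at baseline | Yes | Yes |
| End-of-study level | DTSQs at 12 weeks | No | Yes |
| Difference score = DTSQs at 12 weeks − DTSQs at baseline | DTSQs at both times | No | Yes |
| Perceived change | DTSQc at 12 weeks | Yes | Yes |

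This takes the unnamed baseline DTSQ to be the status version, as the outcome section says it is.

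**Step 3: could the 12-week wording be shorthand for both forms?** The Baseline section uses the generic name, which could cover more than one version. The 12-week section does not; it specifies the change version. The EQ-5D serves as a comparison: the Health status section places it at baseline and at 12 weeks, and both procedure sections agree. The mismatch is therefore confined to the DTSQ.

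**Step 4: could the change form stand in for the missing one?** The outcome section brings in the DTSQc because status scores may already be near their maximum at baseline, and it asks for both forms at 12 weeks. It treats the DTSQc as an addition. The difference score is defined from the status form at two times, so the DTSQc does not supply it.

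**Step 5: who is affected.** The outcome section describes an adult version (18 years and over), a teen version (13 to 17) and a parent version (for teens aged 13 to 15). The requirement for both forms at 12 weeks is written for participants generally; the difference score is named for the parent and teen versions. No version is described for children under 13, although the Nutrition education section provides for participants aged 11 or younger. The number who would have paired status scores is thus not given and cannot be equated with everyone enrolled.

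**The case against.** The strongest reply is that this is a shortened list in a condensed article. The 12-week section does not say that the change form is the sole satisfaction measure. The section that defines the outcome is explicit about both forms, and the unseen schedule may agree with it. On that view the correct instruction is already in the document and only a line of narrative needs tidying.

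Part of this stands. The documents do not show that the status form is omitted in practice, so any loss of data is conditional. Even in the worst case satisfaction is not lost as an outcome, since the DTSQc still measures change and was designed to avoid the ceiling problem. What does not stand is the idea that the mismatch is merely clerical: it determines which data are collected for a secondary outcome, and the procedure section is a natural source for whoever builds the visit.

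A reader might go further and infer that the satisfaction difference is already lost for all of the roughly 500 participants, or that the stated power of more than 90% fails for it. The documents support neither. The first assumes that the questionnaire set was built from the 12-week section alone and that everyone has a DTSQ version. The second applies a general statement about continuous outcomes to an instrument that the statistical section does not mention. Nor do the documents give the scoring of the two forms, so no argument here rests on how their scales compare.

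**Conclusion.** The contradiction is real and is visible in the text of two current sections. Its size is one questionnaire at one visit. If the 12-week section is followed as written, the end-of-study status level and the DTSQs difference score cannot be formed and cannot be recovered; if the outcome section is followed, both can.

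The conclusion rests on two assumptions: that the baseline DTSQ is the status version, as the outcome section states, and that the 12-week list could be used as the instruction for the visit. The schedule could show that the second does not arise in practice, but the text would still need correcting. The perceived-change measure and the primary implementation outcome are unaffected. The point deserves action before 12-week data accumulate, but it does not threaten the main conclusions of the study.

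**What to change.** Amend the 12-week section to name both the DTSQs and the DTSQc, for each age version that the outcome section lists, and align Table 1 if it differs. Confirm that the 12-week questionnaire set actually contains both forms.

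If the status form was deliberately left out at 12 weeks, change the outcome section instead: remove the difference score and the end-of-study level, and state that change in satisfaction is measured by the DTSQc.

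The first option costs one short questionnaire per participant at one visit (the outcome section gives 8 items for adults, 12 for teens and 14 for parents). The second costs nothing to collect but gives up the two status-based results.
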